### Variables

Reviewers in each hospital were provided with a handbook with instructions to follow in the data collection process.-Exposure variables:*Related to the patients’ personal background*: date of birth, sociodemographic variables (level of education, occupation of the patient or of the head of the household, marital status and living arrangements), height, weight, lifestyle habits, gynecological history (family history of gynecological cancer, oral contraceptives or hormonal replacement therapy, first and last menstruation date, menopausal status [pre- or postmenopausal], number of pregnancies and of births, breastfeeding [yes/no and duration]); and comorbidities (Charlson Comorbidity index) [16].*Related to the hospital*: number of beds, whether it is a teaching hospital, catchment population size, number of patients treated for breast cancer annually, and whether it has a breast cancer unit and medical or radiation oncology services.*Related to the process of care*: date of first contact with medical care (scheduled/emergency), time between the first symptoms and the first contact with medical services, time between the first medical appointment and histological diagnosis, time between diagnosis and treatment, and date of diagnosis.*Related to the pre-intervention tumor history*: mode of detection (symptomatic, screen-detected), symptoms (lump, lymph nodule, swelling or hardening of a part of breast, change in the size or shape of the breast, skin retraction, ulceration/wound, pain, secretion, inflammation, nipple retraction), date of the first symptom, clinical TNM classification (cTNM), additional diagnostic tests (ultrasound scan, magnetic resonance imaging [MRI], biopsy, computerized axial tomography [CAT], bone scan, galactography, ultrasound), histological type (infiltrating carcinoma, infiltrating ductal carcinoma, infiltrating lobular carcinoma, mucinous carcinoma, metaplastic carcinoma, intraductal carcinoma, and others) and serum marker levels (CA15-3, CA27.9, CEA, CA125).*Related to neoadjuvant treatment:* chemotherapy (regimen and whether it is completed), radiotherapy, hormone treatment, anti-HER2, and other therapies; and clinical and radiological response (assessed by MRI) categorized as no response (no changes or progression), weak partial response (if the tumor size reduced less than 50%), strong partial response (if the tumor size reduced by 50% or more), and complete response (no residual tumor) [17].*Related to surgery*: date, duration of the intervention, emergency vs scheduled, surgical technique (quadrantectomy, lumpectomy, segmentectomy, simple mastectomy, radical mastectomy, modified radical mastectomy, skin-sparing mastectomy, nipple-sparing mastectomy, contralateral prophylactic mastectomy, lymphadenectomy), time between diagnosis and intervention and/or pre-surgical adjuvant treatment, and intraoperative complications (bleeding, nerve injury, anesthetic complications, allergic reaction to the prophylactic antibiotic, others).*Related to anatomical pathology*: laterality, sentinel node biopsy (yes/no and results), histological type (intraductal, ductal, lobular, tubular, mucinous, medullary, cribriform, papillary, non-specific, others), degree of differentiation, pathological TNM (pTNM), location, size, distant metastases, vascular and nervous infiltration, number of lymph nodes analyzed and number positive, margin involvement, estrogen receptor/progesterone receptor status, Ki-67, P53, CK5/6, CK14, CK19, and HER2 expression, oncotype, and MammaPrint.*Related to admission*: setting (hospitalization vs. or ambulatory surgery), length of hospital stay in days after first intervention, in-hospital complications (seroma, wound infection, necrosis of skin flap, pneumothorax, brachial plexus pathology, and others), reintervention during admission, other medical treatments, and death.*Related to follow-up*: primary treatment: adjuvant postoperative treatment (radiotherapy, chemotherapy, hormone therapy, anti-HER2, and other therapy), date of treatments, reconstructive plastic surgery (yes/no, technique and date), other postoperative treatments (rehabilitation, psychologist/psychiatrist, others), and contact with social services; immediate complications and any reported during the follow-up period: chest wall and breast complications (seroma, post-surgery adhesions, soft tissue necrosis and recurrent skin infections), musculoskeletal (reduced arm mobility), lymphedema, neurological (paresthesias, neuropathy, cognitive dysfunction), pulmonary (pneumonitis, pulmonary fibrosis) cardiovascular morbidity (cardiomyopathy), psychological effects (anxiety), pain, other toxicities (ototoxicity, nephrotoxicity), reproductive health (premature menopause, infertility, sexual dysfunction), osteoporosis, weight gain, mycosis, and immunosuppression (agranulocytosis, lymphopenia); complications after reconstructive surgery (prosthesis infection, capsular contracture, others) and reinterventions, readmissions, death and their respective causes; and management of the disease during the follow-up period: diagnostic tests after surgery (CAT, positron emission tomography-CAT, biopsy, MRI, others), treatments (surgery, radiotherapy, chemotherapy, hormone therapy, anti-HER2, others), and number of follow-up visits per year (to the surgery/gynecology department, oncology department, rehabilitation unit, pain unit and palliative care unit).

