### Sample size calculation

We estimated the sample size based on the objective related to the creation and validation of a predictive model for which a relatively large sample size is required. The literature on prediction models indicates that a minimum of 10 outcome events are needed per predictor (relapse) [24]. Our aim is to include a limited but comprehensive list of variables (likely, not less than 10), in the multivariate regression models. Given this, we estimated that we needed at least 100 events of the dependent variable in the sample in order to ensure that the regression model converges adequately. It has been reported [25] that 7% of patients with breast cancer relapse within the first 2 years and considering this rate, we calculated the estimated sample size. Nevertheless, so far, based on 1456 patients, the relapse rate has been 4%, implying that no more than six variables should be included in the predictive models. We included all consecutive new cases until the sample size was achieved.

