### Statistical analysis

- Descriptive statistics: Mean and standard deviations for continuous variables (or median and interquartile ranges, when the observed variables do not follow a normal distribution) and frequencies and percentages for qualitative variables.-Bivariate analysis:The Student’s t-test or the non-parametric Wilcoxon test (for non-normal distributions) will be applied for two-level outcomes, and ANOVA analysis or a Kruskal–Wallis test (for non-normal distributions) where there are three or more categories in the outcome. Otherwise, for categorical variables, the Chi-square test (or Fisher’s Exact method, where required) will be used. Multivariate models will be used where appropriate to adjust for confounders.-Creation and validation of predicitive models:. Participants will be randomly divided into two groups: the derivation (60%) and validation (40%) cohorts. The study unit will be the patient (each patient being included only once). The predictive model will be created with the derivation group (group 1). Initially, univariate analyses will be performed, to identify variables related to the selected outcomes. Variables with a *p* < 0.20 will be entered into a multivariate logistic regression model, when outcome variables are dichotomous (mortality, re-admissions or relapse, major complications). Statistically significant variables will be included in the final model. Based on its estimated contribution in the multivariate logistic regression model, a score will be assigned to each variable. From this, a severity risk score will be created with the receiver operating characteristic curve. One cut-off point will be selected, namely, that giving the best balance between sensitivity and specificity. For the continuous outcomes (changes in health-related quality of life), a general lineal model will be used. The validity of the model and the score will be tested in the validation sample (group 2) and also in the retrospective sample (group 3). We will calculate the sensitivity, specificity, and area under the receiver operating characteristic curve (AUC), and *p* values for comparisons of AUCs between the groups. The models will be calibrated using the Hosmer-Lemeshow test. A multilevel analysis will be performed with patients (level 1) nested within hospitals (level 2).

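### Univariate screening and significance-based retention on about 35 derivation relapses will give an optimistic score, and no rule keeps follow-up events out of the candidate predictors

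*Protocol article*

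**What the plan says.** Selection rule (Statistical analysis). The cohort is split first: "Participants will be randomly divided into two groups: the derivation (60%) and validation (40%) cohorts". In the derivation part, "univariate analyses will be performed, to identify variables related to the selected outcomes". Variables with p below 0.20 "will be entered into a multivariate logistic regression model, when outcome variables are dichotomous (mortality, re-admissions or relapse, major complications". Then: "Statistically significant variables will be included in the final model". The significance level for retention is not given. The section names no candidate list and no time by which a predictor must be known.

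Event budget (Sample size calculation). The rule is "a minimum of 10 outcome events are needed per predictor (relapse". From this the authors concluded that "we needed at least 100 events of the dependent variable in the sample", using an expected 7% relapse rate at two years. The same section reports 4% so far among 1456 patients and lowers the ceiling to six variables.

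Variable list (Variables). Under the label of exposure variables, the block on follow-up contains "reinterventions, readmissions, death and their respective causes; and management of the disease during the follow-up period" and "number of follow-up visits per year (to the surgery/gynecology department, oncology department, rehabilitation unit, pain unit and palliative care unit", together with complications recorded during follow-up. Death also appears in the block on admission. The outcome list in the same section names complications, recurrence and death.

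Validation. The abstract names split validation and bootstrapping. The Statistical analysis section adds testing in the 40% sample and in the retrospective cohort, with AUC comparisons between groups.

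**The concern.** Two separate problems meet in this modelling plan.

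The first is optimism. When many variables are tested one at a time against few events, some pass by chance, and the variables kept are those whose effects happened to be overestimated in this sample. A ten-events rule applied to the variables left at the end does not count the candidates that were tried and discarded. The score then looks better in the derivation data than it will in new patients, and its predicted risks are too extreme.

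The second is the boundary between predictors and outcomes. Some items labelled as exposures occur after the time at which a prediction would be made, or are themselves the outcome. If such an item were admitted, it would be strongly associated with relapse or death because it follows from them, and it would not be available when the score is used.

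The stakes are practical. The sample size was set on this objective, and the section on expected outcomes intends the tool to inform physicians and patients about individual risk at appointments.

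**Working it through.** **Step 1. Reproduce the plan's figures.** Inputs from Sample size calculation: 1456 patients, 7% expected and 4% observed relapse, ten events per predictor.

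- Planned size: 100 / 0.07 = 1428.6, so 1429 patients. At 7%, 1456 × 0.07 = 101.9 events. This agrees with the stated aim.
- Cap: 1456 × 0.04 = 58.2 events; 58.2 / 10 = 5.8. The stated six is reached by rounding up; applied strictly, the rule gives five.

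**Step 2. Apply the same rule to the women who build the model.** The 60% comes from Statistical analysis.

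- Derivation: 0.60 × 1456 = 873.6, so 874 women; 874 × 0.04 = 35.0 relapses; 35.0 / 10 = 3.5, so three variables.
- Validation: 1456 − 874 = 582 women; 582 × 0.04 = 23.3 relapses.

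This step uses only the article's own numbers. Event rates for mortality, readmission and major complications are not given, so the count applies to relapse only.

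**Step 3. What the 0.20 screen lets through.** The article does not state the number of candidates k, so 30, 60 and 100 are assumed. If all candidates were independent noise, the number passing would be binomial with mean 0.20 × k.

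| k | Derivation relapses per candidate (35/k) | Mean noise variables passing | Chance that 7 or more pass |
|---|---|---|---|
| 30 | 1.17 | 6 | 39% |
| 60 | 0.58 | 12 | 97% |
| 100 | 0.35 | 20 | >99.9% |

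**Step 4. The whole procedure, simulated.** Assumptions: 874 derivation and 582 validation women, 4% events, independent normal candidates, four true predictors with log-odds 0.6, 0.5, 0.4 and 0.3 per SD, entry at p<0.20, retention at p<0.05, refit, 300 runs per setting. The six-variable cap was not imposed.

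| k | Final variables | Of which noise | AUC derivation | AUC validation | Median calibration slope |
|---|---|---|---|---|---|
| 30 | 3.9 | 1.3 | 0.76 | 0.68 | 0.66 |
| 60 | 5.7 | 3.0 | 0.79 | 0.67 | 0.52 |
| 100 | 7.7 | 5.1 | 0.83 | 0.65 | 0.37 |

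For scale, the AUC of the true model in this setting is about Φ(√(0.6² + 0.5² + 0.4² + 0.3²) / √2) = Φ(0.927 / 1.414) = 0.74. The validation AUC therefore falls short by about 0.06 to 0.09; the rest of the gap to the derivation AUC is false apparent performance. With no true predictors and k = 60, a model is still produced in 97% of runs, with AUC 0.69 in derivation and 0.50 in validation.

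**Step 5. Predictor and outcome labels side by side.**

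| Item | Exposure list in Variables | Outcome elsewhere |
|---|---|---|
| Death | Admission and follow-up blocks | Outcome list; mortality is a modelled outcome |
| Readmissions | Follow-up block | Modelled outcome |
| Complications in follow-up | Follow-up block | Outcome list; major complications are modelled |
| Treatments in follow-up; pain and palliative care visits | Follow-up block | Not outcomes, but can result from relapse |

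No sentence says which of these may be candidates. If one were admitted, it would be present in both random halves, so the split would confirm the inflated performance and not expose it.

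**The case against.** The strongest reply on leakage is that it is inferred. A reader might conclude from the exposure list that the score will contain death or palliative care visits. The article does not support that. The Statistical analysis section never says that the full list feeds the screen, and the sample size section speaks of a limited one. The list also serves the cost analysis and the study of treatment variability, which need follow-up visits and treatments. Death, complications and recurrence are plainly named as outcomes. A condensed article may leave the exact candidates to the full protocol or analysis plan. This reply stands: leakage is not excluded, but it is not established either. The double labelling of the same items remains.

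On overfitting, the reply is that safeguards exist: a six-variable cap, a 40% validation sample, bootstrapping, a retrospective sample, AUC comparisons and a commitment to TRIPOD reporting. These count, and a gap such as 0.79 against 0.67 is what the validation is meant to show. But they detect or report optimism; they do not remove it. The cap limits final size only. The validation cohort has about 23 relapses, so its estimates will be imprecise. Bootstrapping is named in the abstract but given no role in the Statistical analysis section.

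A further reply is that the simulated sizes are scenario-specific, which is true. With three stronger predictors (log-odds 0.9, 0.6 and 0.4 per SD, also assumed) and 20 to 60 candidates, AUC in new patients was 0.74 to 0.76 against a best attainable 0.78, a much smaller loss. A reader should not take a fixed share of noise variables, or a single AUC gap, as a prediction for this study.

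**Conclusion.** The concern holds in two parts of different strength.

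The selection rule is fixed in the text and is poorly suited to the events available. That the derivation cohort has about 35 relapses and supports about three variables under the plan's ten-events rule, not six, follows from the article's figures alone. The direction of the bias, towards optimism, is the same for every candidate count in the table. Its size is conditional: for 30 to 100 candidates with four modest true predictors, derivation AUC is 0.76 to 0.83, validation AUC 0.68 to 0.65 and calibration slope 0.66 to 0.37. The independence of candidates, the 0.05 retention level, the candidate counts and the effects are all assumptions.

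The second part is a gap in the wording. Items labelled both exposure and outcome, with no stated prediction time, leave post-baseline variables open as candidates. No inflation of the AUC can be attributed to this from the documents.

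**What to change.** 1. State the prediction time for each model and admit only variables known by then. Separate the follow-up items, and death in the admission block, from the candidate predictors; they can stay in the data set for the cost and variability aims.
2. Replace the p<0.20 screen and the significance-based removal with a short list fixed in advance on prior clinical knowledge, counted in parameters.
3. Fit that list with penalisation. Preferably use all 1456 women with bootstrap optimism correction: about 58 relapses, so at most five to six parameters under the plan's own rule (five if applied strictly). If the 60/40 split is kept, restate the cap as about three.
4. Keep the retrospective cohort as a separate validation sample.

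This changes wording only and needs no new data. The price is a lower apparent AUC and fewer exploratory variables in the score. Using all women for model building also gives up the internal hold-out sample, which with about 23 relapses would have been imprecise.

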## Background

Prevalence of breast cancer remains high worldwide [1]. Mortality rates have been decreasing since the 1970s. Screening programs and advences in adyuvant therapy have contributed to decrease mortality and this pathology has become in a chronic disease. l [2]. On the other hand, the development of new biomarkers and other diagnostic tools and new therapies could lead to a greater variability in clinical practice.

Several decision tools have already been created with the aim of predicting overall 5 or 10 year and disease-free survival [3–5]. In addition, with the increase in the life-expectancy in these women, it has become important to assess quality of life [6–8]. On the other hand, the course of breast cancer may be influenced by variables not directly related to the breast, such as other comorbidities and treatments [9–11].

This research was designed under the auspices of the Health Services Research on Chronic Patients Network (REDISSEC). This network was created to focus on three major issues: the challenge of managing the phenomenon of chronicity, the desire for more and better information, and a need to increase research capacity in the fields of health policies and services in Spain [12]. The overall objective of the CAMISS (abbreviation from the Spanish for health services research in breast cancer) research project is to evaluate the health services received by patients with breast cancer from screening, diagnosis and treatment to prognosis (complications, survival, and quality of life).

[name] et al. conducted the CAMISS-Retrospective study, which included 1086 women with breast cancer from a population-based screening program. These women were diagnosed with breast cancer between 2000 and 2008 and were followed-up to December 2013. The main objective of that study was to assess the impact of the mode of detection (screen-detected cancer vs. interval breast cancer) on overall survival and disease-free survival. Notably, however, symptomatic women were not included in this retrospective cohort and data were not collected on quality of life [13].

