### Study population

Women older than 18 years with an incident breast tumor will be included. The breast cancer diagnosis considered will be that reached after a biopsy of the tumor, including cases of ductal carcinoma in situ, invasive ductal carcinoma, tubular carcinoma, mucinous carcinoma, papillary carcinoma, cribriform carcinoma, invasive lobular carcinoma and lobular carcinoma in situ.

Symptomatic breast cancer will be included, as well as screened and interval breast cancer. The breast cancer screening program is public and universal in Spain. Following the recommendations of the European Guidelines for Quality Assurance in breast cancer screening and diagnosis [14], the Spanish Breast Cancer Screening Program provides free biennial screening to women who are between 50 and 69 years old. Recently, women aged from 45 to 49 years and 65 to 69 years are being incorporated into screening programs. Interval breast cancer is defined as primary breast cancer diagnosed in a woman who had a screening test, with or without further assessment, with a negative result, and diagnosed well before the next invitation to the screening test or before a period of time equal to the screening interval in a woman who has reached the upper age limit for screening [15].

Exclusion criteria are: diagnosis of sarcoma, lymphoma or inflammatory carcinoma; breast cancer recurrence; terminal illness; and a severe mental or physical condition or any other factor which interferes with the woman’s ability to complete the questionnaires. In addition, in situ carcinomas will be excluded from the survival analysis.

Socio-demographic and clinical data will be collected on women lost to follow-up. Figure 1 represents flow-chart of the recruitment and Table 2 represents data collection in participant centers.

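### The planned AUC p values against the retrospective sample mix case mix with score validity, so neither a significant nor a non-significant result shows whether the score carries over

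*Protocol article*

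**What the plan says.** All references are to the protocol article.

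- **Statistical analysis.** The prospective cohort is split at random into derivation (60%, group 1) and validation (40%, group 2). The model and score "will be tested in the validation sample (group 2) and also in the retrospective sample (group 3"). Sensitivity, specificity and AUC are reported in each, with p "values for comparisons of AUCs between the groups" and a Hosmer-Lemeshow test. The AUC comparison is not restricted or standardised, and no significance level or pass/fail rule is given.
- **Table 1.** Validating the rules in a retrospective sample from early detection programmes is a named objective.
- **Background.** The retrospective study has 1086 women from a screening programme, diagnosed 2000–2008 and followed to December 2013. It compared screen-detected with interval cancers, and "symptomatic women were not included in this retrospective cohort".
- **Study population.** For the prospective cohort, "Symptomatic breast cancer will be included, as well as screened and interval breast cancer".
- **Sample size calculation.** The plan assumed that "7% of patients with breast cancer relapse within the first 2 years" and that "we needed at least 100 events of the dependent variable in the sample". It then reports that "based on 1456 patients, the relapse rate has been 4"%, "implying that no more than six variables should be included in the predictive models".

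**The concern.** The objective asks whether the score works in group 3. The planned p value answers a different question: whether the AUC is the same in two groups of women recruited in different ways. AUC is the chance that a woman with the event has a higher score than a woman without it. It rises when a sample mixes very low and very high risks and falls when risks are similar, even if every coefficient is right in both samples. A mode of detection present in one sample and absent from the other is a plausible reason for the spread to differ.

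The p value can therefore mislead in two ways. A correct score can look worse in group 3 only because the population is narrower. Equal AUCs, or a difference too small to detect, can be read as successful validation when they do not establish it. The second risk is the larger one here, because the prospective groups contain few relapses.

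**Working it through.** **1. The plan's own figures.** 10 events × 10 predictors = 100 events. 100 / 0.07 = 1429 patients, in line with the 1456 reported. At 4%, 1456 × 0.04 = 58.2 relapses, and 58.2 / 10 = 5.8, the plan's six variables. The sizing reproduces. The article gives no figure for the AUC comparison.

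**2. Events per group.**
- Group 1: 0.60 × 1456 = 874 women, × 0.04 = 35 relapses.
- Group 2: 0.40 × 1456 = 582 women, × 0.04 = 23 relapses.
- Group 3: 1086 women. Its event count is not given; at an assumed 4% it is 43.

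**3. Effect of spread on AUC when the score is correct.** Assume a logistic model with a normal linear predictor of standard deviation σ and the same coefficients in both samples. For a rare outcome, AUC ≈ Φ(σ/√2). AUC 0.75 needs Φ⁻¹(0.75) = 0.674, so σ = 0.674 × 1.414 = 0.954. With σ 20% narrower, Φ(0.8 × 0.674) = Φ(0.540) = 0.705. With 30%, Φ(0.472) = 0.682. With 50%, Φ(0.337) = 0.632. Exact calculation at 4% events gives 0.707, 0.684 and 0.634.

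**4. Precision.** The Hanley-McNeil variance, with m events and n non-events, is

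[A(1−A) + (m−1)(A/(2−A) − A²) + (n−1)(2A²/(1+A) − A²)] / (mn).

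Group 2, with A = 0.75, m = 23, n = 559: [0.1875 + 22 × 0.0375 + 558 × 0.0804] / 12857 = 45.9 / 12857 = 0.00357, so SE ≈ 0.060. Group 3, with A = 0.684, m = 43, n = 1043: SE ≈ 0.046. The SE of the difference is √(0.060² + 0.046²) ≈ 0.075. For 80% power the drop must be about (1.96 + 0.84) × 0.075 = 0.21. The drops expected from 20–30% narrowing at AUC 0.75 are 0.043 and 0.066. A non-significant result is therefore the likelier outcome.

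**5. Chance that a correct score is found significantly worse in group 3.** By the same approximation, 30% narrowing at AUC 0.75 gives Φ(0.066/0.075 − 1.96) = Φ(−1.08) = 0.14. Simulation with DeLong variances gives somewhat higher rates (0.195 for this case). Setup: n = 582 vs 1086, two-sided 5% assumed, 1000 replicates per cell. The ranges below cover prospective AUC 0.70, 0.75 and 0.80. Column heads give the event rate in group 2 / group 3.

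| σ in group 3 | 4% / 4% | 4% / 10% | 12% / 12% |
|---|---|---|---|
| equal | 3–4% | 4–6% | 2–3% |
| 20% narrower | 9–16% | 12–22% | 15–25% |
| 30% narrower | 14–25% | 18–35% | 27–48% |
| 40% narrower | 22–42% | 26–52% | 43–75% |
| 50% narrower | 28–58% | 37–67% | 58–91% |

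Only the 4% prospective rate comes from the article. The 10% and 12% columns stand for a longer horizon, which is possible because group 3 was followed to December 2013.

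**6. Group 1 as comparator.** The Hanley-McNeil rates for 20–30% narrowing at 4% in both groups are 8–21%. That treats the score as known. In practice it is fitted to about 35 relapses, so a drop from group 1 to group 3 also contains optimism, a further cause that the p value cannot separate.

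**The case against.** Several points on the other side are sound.

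- **Group 3 is openly restricted.** Table 1 says its patients come from early detection programmes. Lower discrimination there is real information for users of the score in that population. This stands, and it is why the group 3 AUC should still be reported. It does not rescue the between-group p value, which cannot say why the AUCs differ.
- **The p value is one item among several.** Sensitivity, specificity and calibration are also planned, the article commits to TRIPOD reporting, and no rule turns a significant difference into a failed validation. A reader might infer that the p value decides the objective and that a sound score would be discarded. The article does not say so.
- **The rejections are not type I errors of the stated null.** When spreads differ, the true AUCs differ, and rejecting equal AUC is correct. The error lies in reading that rejection as evidence against the score.
- **Spread and direction are unknown.** Group 3 keeps interval cancers. In the prospective cohort stage IV is only 18 + 11 = 29 of 1456 women (2%), and in situ cases are excluded from the survival analysis. Narrowing is plausible but not shown.
- **An article condenses.** Details of standardisation can sit in a fuller document. The comparison itself is stated here, however, and the mismatch follows from what the article says about the two cohorts.

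**Conclusion.** The point holds in a limited form. The article commits to AUC p values between groups whose case mix differs by design, and such a p value cannot separate score validity from population difference in either direction.

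A reader might go further and infer that a correct score will often be found significantly worse in group 3. The article does not support that. At its 4% relapse rate and a 20–30% narrowing, this happens in about 9–25% of studies: above the nominal 2.5% in that direction, but a minority. It exceeds half only with a 40–50% narrowing combined with a high AUC or more events than the article reports. With about 35 and 23 relapses in groups 1 and 2, a non-significant difference is the likelier result, and it would not show that the score carries over.

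The rates assume a normal linear predictor, a score equal to the true predictor, AUC 0.70–0.80, two-sided 5% testing, and assumed spreads and event rates in group 3. The mismatch in case mix needs none of these assumptions. The change is worth making because it costs little and bears on a named objective.

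**What to change.** 1. Drop the p value for AUC comparisons with group 3. Report the observed group 3 AUC with its 95% CI beside the AUC expected there if the score were correct (model-based concordance, computed from the score's own predictions in group 3).
2. Report the calibration slope in group 3, and judge whether the score carries over from the observed-minus-expected AUC and the slope together.
3. As a supportive check only, compare group 3 with the screen-detected plus interval cancers of the prospective validation group, at the same follow-up horizon. Interval cancers should be identified by the definition under Study population. The Variables section codes mode of detection only as symptomatic or screen-detected, so selecting women without symptoms could remove the interval cancers and create a new mismatch.

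Cost: a change of wording and a short calculation on data already held. The matched subset in step 3 will have fewer than the roughly 23 relapses of group 2, so its estimate will be imprecise and should not decide the question.
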